**Fig. 1 Fig1:**
[figure not shown]
Study Flow

Due to the nature of the intervention, blinding of the participating legal representatives and the researchers conducting the education program is not possible. Independent persons and an external biometrician, blinded to the group allocation, will perform data entry and data analysis, respectively.

#### Control group (CG)

As no equivalent intervention is available, the control group (CG) will receive standard care. After data collection is completed (e.g., after the six-month follow-up), CG participants will be invited to take part in the education program.

### Outcomes

The primary outcome measure is *knowledge*, which is operationalized as an understanding of decision-making processes in healthcare affairs and in setting realistic expectations regarding probabilities of benefits and harms of PEG, PR and AP to people with dementia.

Secondary outcome measures are: 1) legal representatives have obtained sufficient knowledge (using a cut-off of 70% correct answers in the knowledge test); 2) legal representatives have obtained sustainable knowledge, which is measured 6 months after intervention; 3) percentage of persons concerned affected by PEG, FEM or AP during follow up of 6 months; and 4) result of the first decision after intervention regarding PEG, PR and AP for the persons concerned including time to first decision.

### Data collection

In the T0 baseline, data of legal representatives will be assessed according to age, gender, education status, activity status (professional or voluntary representative), time since appointment as legal representative and number of persons concerned. Additionally, baseline data and baseline outcome measurements of persons concerned will be assessed. For this, legal representatives will receive a pseudonymization list, documentation sheets and a standardized written introduction. A pseudonymization number will be assigned to each person concerned with dementia. All data will be given to the study site under this pseudonym. The legal representative, using data extracted from routine documentation, will fill in the documentation sheets. The age range, gender, diagnosis additional to dementia, presence of PEG, number and types of PR, name and dosage of antipsychotics will be assessed by multiple choice and free-response questions. Copies of the routine documentation (e.g., a list of drug prescriptions) will be passed on only if pseudonymization is safeguarded.

At T1, the primary outcome *knowledge* will be assessed (Table 1). To assess understanding and realistic expectations, a novel questionnaire was developed based on Bloom’s taxonomy [40], the *User Manual–Realistic Expectations* [41], the contents of the education program, and the evidence-based information for PEG, PR and AP in people with dementia. The questionnaire comprises 13 items: two items on the understanding of decision-making processes in healthcare affairs; two items on quality and validity of study results; and nine items on realistic expectations regarding probabilities of benefits and harms of PEG, PR and AP to people with dementia (with three items per intervention). All items are multiple choice questions with four choices, with only one correct answer. Questions with more than one answer and unanswered questions will count as a wrong answer. No summarizing score is given if four or more of the 13 questions remain unanswered.

**Table 1 Tab1:** Data collection

Outcomes	Measures	Follow-up
Knowledge	Questionnaire developed on the basis of evidence-based information and contents of the education program	T1, T3
First decision PEG	Standardised telephone interview	T2, T3
First decision PR	Standardised telephone interview	T2, T3
First decision AP	Standardised telephone interview	T2, T3
Physical restraints	Documentation sheet; medical and nursing records	T3
Antipsychotics	Documentation sheet; medical and nursing records	T3
PEG	Documentation sheet; medical and nursing records	T3

T1 = at the end of / up to 2 weeks after the intervention; T2 = 3 month follow-up; T3 = 6 month follow-up

Legal representatives in the IG will receive the test at the end of the education program. They may complete the test immediately or return it by mail in the following 2 weeks. Participants in the CG will receive the test by mail at the same time.

At T2 (the 3-month follow-up), the results of the first decisions regarding PEG, PR and AP for the persons concerned will be assessed (Table 1). Decisions may have been initiated by legal representatives themselves (e.g., consultation for medication review), by relatives (e.g., worries about agitation) or by health professionals (e.g., required consent for PEG or PR). We define a decision as every consideration about PEG, PR or AP, regardless of the result.

Participants receive a documentation sheet for each intervention at the beginning of follow-up to assess the starting point of the decision-making process, presence of the intervention before and after the decision, reason or trigger for decision-making and changes regarding the intervention. The sheets may be used for personal documentation only or may be sent back to the study center.

Participants will be contacted by phone to ask if they had made a decision regarding PEG, PR and/or AP. If they had made a decision, they will either be reminded to fill out and return the documentation or directly interviewed by telephone to fill out the sheet. The first decision of each intervention will be recorded and classified in one of the four following categories, whereby 0 = no presence and 1 = presence of PEG, FEM and AP:

Category I: 0 ➔ 0 (No PEG / FEM / AP ➔ decision ➔ no PEG / FEM / AP).

Category II: 0 ➔ 1 (No PEG / FEM / AP ➔ decision ➔ new PEG / FEM / AP).

Category III: 1 ➔ 1 (PEG / FEM / AP ➔ decision ➔ still PEG / FEM / AP).

Category IV: 1 ➔ 0 (PEG / FEM / AP ➔ decision ➔ no longer PEG / FEM / AP).

The date of the decision will be documented.

At T3 (the 6-month follow-up), the sustainable knowledge of legal representatives will be assessed using the same test as at T1.

Additionally, the number of PEG, PR and AP interventions in the persons concerned will be assessed (Table 1). The legal representatives will perform the assessment as at T0, filling out the documentation sheets and forwarding any copies of routine documentation. New diagnoses since baseline, the presence of PEG, the number and types of PR, medication data and decisions made about one of these interventions will be documented.

All persons concerned who are represented by one of the participating legal representatives at least for 2 weeks within the 6-month follow-up are eligible. If a person concerned who was assessed at T0 is no longer represented by the participant prior to end of follow-up, a documentation sheet will be filled out. The time of and reason for dropout, as well as the presence of PEG, number and types of PR and medication data at the time of dropout, will be documented. New persons concerned during the study period will be assessed at the time of inclusion and at T3. At the time of inclusion, a documentation sheet will be filled out, including time of inclusion, age range, gender, any diagnoses additional to dementia, the presence of PEG, number and types of PR and medication data.

Participants will receive the knowledge test and documentation sheets by mail or, if requested, by email. Participants in the CG have to submit the documents before subsequently beginning the education program (they may hand them over in person on the first training day).

Participants who had not made all three decisions regarding PEG, PR or AP for a person concerned at T2 will be additionally contacted by phone and asked again if they had made a decision since T2. Results of the first decision of each intervention will be recorded as in T2.

To reach a high compliance rate until T3, participants will receive stamped, addressed envelopes for returning outcome assessments by mail. Submission of all documents to the study center will be also possible by email or fax. If required, participants will be reminded by phone, and any of their questions about data assessment will be answered.

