**Methods:**

A randomized controlled trial with a six-month follow-up will be conducted to compare the PRODECIDE education program with standard care, enrolling legal representatives (*N* = 216). The education program lasts 10 h and comprises four modules: A, decision-making processes and methods; and B, C and D, evidence-based knowledge about PEG, PR and AP, respectively.

The primary outcome measure is *knowledge*, which is operationalized as the understanding of decision-making processes in healthcare affairs and in setting realistic expectations about benefits and harms of PEG, PR and AP in people with dementia. Secondary outcomes are sufficient and sustainable knowledge and percentage of persons concerned affected by PEG, FEM or AP. A qualitative process evaluation will be performed. Additionally, to support implementation, a concept for translating the educational contents into e-learning modules will be developed.

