## Discussion

In this RCT, we will evaluate the efficacy of the PRODECIDE education program in the context of training for legal representatives.

The PRODECIDE study has several strengths. Legal representatives will be allocated to the intervention or to the control group using a computer-generated randomization scheme. An independent person not involved in either the study or data collection will perform the allocation. Data entry will be performed blinded. Various approaches will be taken to reduce missing data and dropouts. These strategies were adapted from previous RCTs with very low attrition rates [20, 60, 61]. For analysis, the intention to treat principle will be used.

The study limitations include the fact that, due to the nature of the intervention, neither participants nor researchers conducting the education program and data collection will be blinded. Likewise, it is not possible to safeguard either the inclusion of all eligible persons with dementia or the correct documentation of PEG, PR and AP for all persons concerned. Only the legal representatives will perform the assessment for eligibility, and they will give the data of the persons concerned to the study center under a pseudonym. We assume that the error ratio will be comparable in IG and CG. Nevertheless, it is possible that enhanced knowledge in the IG leads to a more correct documentation and to a bias of results. Data collection will be verified by using medical and nursing records if possible. Finally, legal representatives are well connected, for instance through office partnerships or supervision sessions, such that “contamination” from the intervention to the control group by sharing educational materials is possible. However, as the training is both hands-on and in-depth, we do not expect that the CG has an improved knowledge solely on the basis of written educational materials.

At the end of this study, information about the efficacy of the PRODECIDE education program, the usability of e-learning modules and processes that interfere with or promote a successful implementation into the regular training curricula for legal representatives will be available.

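### The antipsychotic outcome may be recorded differently in the two arms at T3, because it is unclear whether representatives, by then trained in the intervention group only, select the drugs themselves

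*Protocol article*

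**What the plan says.** All places are in the protocol article.

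- **Who records.** Data collection: "The legal representative, using data extracted from routine documentation, will fill in the documentation sheets". The Background says that representatives seldom hold a health-care qualification. Randomization and blinding says that they cannot be blinded.
- **What is recorded at T0.** Data collection: "presence of PEG, number and types of PR, name and dosage of antipsychotics will be assessed by multiple choice and free-response questions".
- **What is recorded at T3.** Data collection: "The legal representatives will perform the assessment as at T0, filling out the documentation sheets and forwarding any copies of routine documentation". The next sentence describes the content more broadly: "the presence of PEG, the number and types of PR, medication data and decisions made about one of these interventions will be documented". The records for persons who leave and for persons newly taken on also refer to medication data.
- **Second source.** Table 1 lists medical and nursing records beside the documentation sheet for antipsychotics at T3. Copies are conditional: "Copies of the routine documentation (e.g., a list of drug prescriptions) will be passed on only if pseudonymization is safeguarded".
- **Training.** The Abstract describes the last three modules as "B, C and D, evidence-based knowledge about PEG, PR and AP, respectively". Under Data collection, control participants hand in their T3 documents before they start the course.
- **Acknowledged limitation.** The Discussion first assumes similar documentation error in both arms, then allows that "it is possible that enhanced knowledge in the IG leads to a more correct documentation and to a bias of results". Its remedy is: "Data collection will be verified by using medical and nursing records if possible".
- **Analysis.** Data analysis fits a linear model to the percentage of affected persons per representative, with group and the T0 value as independent variables.

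**The concern.** The T0 wording asks for antipsychotics, not for all drugs. Read literally, a person without health-care training looks through the routine documentation and decides which entries qualify. If T3 works the same way, the recorder is untrained in both arms at T0 and in the control arm at T3, but has been taught about antipsychotics in the intervention arm at T3. The instrument's sensitivity could then depend on the intervention under test.

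At stake is the antipsychotic part of the secondary outcome on persons concerned. It serves the further objective in the Objectives section: whether educating representatives leads to a clinically relevant reduction in the three interventions. Differential recording could hide such a reduction or distort its size. The knowledge outcome at T1 does not depend on these sheets.

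**Working it through.** **Plan's own figure.** The article gives no target difference or sample size for the antipsychotic outcome. Its only sample-size calculation is for knowledge. With a difference of 0.085, SD 0.17, 5% two-sided and 90% power, the t-test needs 85.03, rounded up to 86 per group. Then 86/0.8 = 107.5, rounded up to 108 per group, or 216 overall. This reproduces, but does not bear on the present point.

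**Step 1: what T3 measures.** Two readings are open.
- *T3 repeats the T0 item.* The representative selects the antipsychotics, and only the intervention arm has had the antipsychotic module.
- *T3 takes a full drug list.* Recognition by the representative then matters much less at T3. However, T0 and T3 use different instruments, although T3 is said to be done as at T0. The article does not say who sorts the list. The blinding it describes covers data entry and analysis.

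**Step 2: can the T0 adjustment help?** Let *p* be true prevalence, *s* the probability that a true antipsychotic user is recorded as one, and specificity 1. The expected recorded percentage is *p* × *s*. At T0 both arms have the same untrained *s*, so randomization balances the recorded T0 value in expectation and the adjustment moves the group difference by zero on average. At T3, under the first reading, the expected difference (IG − CG) is

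*p*(IG) × *s*(IG) − *p*(CG) × *s*(CG).

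With no true effect this is *p* × [*s*(IG) − *s*(CG)]. The T0 value carries no information on a change in *s* that occurs afterwards in one arm.

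**Step 3: illustration.** The 30% is rounded from the Background's figure of almost 30%, which refers to nursing home residents and not to this trial's population. Every recognition value below is an assumption; none is in the document. A true relative reduction is fully hidden when it equals 1 − *s*(CG)/*s*(IG). The fourth column assumes a true 20% relative reduction, 30% to 24%, which is −6.0 points.

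| *s* CG / IG | Recorded CG / IG, no true effect | Spurious difference | Recorded difference when truth is −6.0 | Reduction fully hidden |
|---|---|---|---|---|
| 0.90 / 0.95 | 27.0% / 28.5% | +1.5 | 22.8 − 27.0 = −4.2 | 5.3% |
| 0.80 / 0.90 | 24.0% / 27.0% | +3.0 | 21.6 − 24.0 = −2.4 | 11.1% |
| 0.80 / 0.95 | 24.0% / 28.5% | +4.5 | 22.8 − 24.0 = −1.2 | 15.8% |
| 0.80 / 1.00 | 24.0% / 30.0% | +6.0 | 24.0 − 24.0 = 0.0 | 20.0% |
| 0.80 / 0.80 | 24.0% / 24.0% | 0.0 | 19.2 − 24.0 = −4.8 | none |

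Gaps of 0.05 to 0.20 thus give 0.30 × 0.05 = 1.5 to 0.30 × 0.20 = 6 points. If recording were instead less complete in the intervention arm, the sign reverses: 0.95 (CG) and 0.90 (IG) give 27.0 − 28.5 = −1.5 points. The last row shows that equal sensitivity shrinks an effect but neither reverses nor hides it.

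**The case against.** A reader might infer that representatives must recognise antipsychotics in order to record them at T3, that the course does change this ability, and that a real reduction will be masked. The document does not support so firm a reading:

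- The restricted wording stands only for T0. For T3, exit and inclusion the text speaks of medication data. If that means the complete drug list, most of what is needed is already in place.
- Table 1 names medical and nursing records as a source, and a prescription list is the article's own example of a copy. No coverage figure is given, so the pseudonymization condition does not show that copies will be scarce.
- The sheet and its written introduction are not shown, and an article need not reproduce them. Multiple-choice items could list drug names and so prompt recognition.
- Module D is described as evidence-based knowledge about antipsychotics. Nothing says that it teaches how to identify them on a medication chart.
- The direction is open. Unblinded representatives who have been taught about harms might also report less use.
- The authors already disclose the possibility of differential documentation, and only a secondary outcome is involved.

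All of this stands, and it limits the point to a possible difference of unknown size and sign. It does not remove the point. The T0 and T3 descriptions do not agree, the record check is conditional, and a disclosed limitation that a small change to the form could avoid is better avoided. The Discussion's working assumption of similar error in both arms also sits uneasily with the bias it then concedes.

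**Conclusion.** The point holds as a possibility that the present wording leaves open. At T3 the antipsychotic outcome may be recorded with different completeness in the two arms, and neither the T0 adjustment nor the conditional record check reliably removes that. If untrained representatives under-record, a true reduction would tend to be diluted or hidden.

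The illustrative 1.5 to 6 points rest on 30% prevalence, perfect specificity and a recognition gap of 5 to 20 points in favour of the intervention arm. The two recognition assumptions have no basis in the document, and the prevalence comes from a different population. If recording is nearly complete in both arms, the bias is small. The primary outcome and its sample size are untouched. The change is worth making because it is cheap and protects an outcome tied to a stated objective.

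**What to change.** Reconcile the T0 and T3 descriptions in Data collection. At T0, inclusion, exit and T3, have the representative transcribe all current medication (name and dose) without selecting antipsychotics. Have the data-entry staff who are already blinded to allocation classify the entries against a drug list fixed in advance. If the physical-restraint item is not already a closed list, use the same closed device checklist at every time point, so that representatives do not have to judge what counts as a restraint.

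The cost is a revised sheet, somewhat longer transcription for representatives and a short coding step for existing staff.

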### Data analysis

Data will be entered into a SPSS database and double-checked by student assistants blinded to the group allocation. Simple plausibility checks will be done in the study center before the final statistical analysis by the statistician. Analysis of all quantitative data will use the intention-to-treat principle. Missing values in primary and secondary outcomes will be imputed using simple methods. A dropout analysis comparing baseline parameters between the study population and early dropouts (before T2) will be performed.

All statistical tests are two-sided using a significance level of 5%. Baseline parameters are described by frequency tables, means, standard deviations or quartiles.

The primary outcome is the percentage of correct answers for the knowledge test at T1. Assuming approximate normal distribution, the expected values from the IG and CG will be compared with adjustment for stratified randomization by professionals and volunteers using bifactorial analysis of variance (linear model). Distribution assumptions will be investigated by graphical methods. Furthermore, interactions between intervention and professional status will be included in a secondary model. Different effects depending on the professional status will be discussed.

The secondary outcome of sufficient knowledge (binary) at T1 will be compared between IG and CG using bivariate logistic regression, including IG/CG and professional status as independent variables. Additionally interactions between intervention and professional status will be investigated in a second model.

The sustainability of knowledge will be investigated at T3. The time course of the knowledge between T1 and T3 will be analyzed by fitting a linear mixed model: the dependent variable is knowledge (% of correct answers), and the independent variables are IG/CG, time (T1, T3), interaction between intervention and time, professional status and interaction between intervention and professional status. To adjust for repeated measurements of the legal representatives, random effects are included (covariance pattern model with covariance structure compound symmetry).

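### A returned knowledge test with four or more blanks gets no score and falls to imputation, although it cannot reach the 70% cut-off, so a certain 'not sufficient' can be imputed as something else

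*Protocol article*

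**What the plan says.** Four statements in the protocol article bear on this point.

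- Data collection, on test length and blanks: "The questionnaire comprises 13 items", and "Questions with more than one answer and unanswered questions will count as a wrong answer".
- Data collection, in the next sentence: "No summarizing score is given if four or more of the 13 questions remain unanswered".
- Outcomes, on secondary outcome 1: sufficient knowledge is defined "using a cut-off of 70% correct answers in the knowledge test".
- Data analysis: "The primary outcome is the percentage of correct answers for the knowledge test at T1"; "Analysis of all quantitative data will use the intention-to-treat principle"; and "Missing values in primary and secondary outcomes will be imputed using simple methods".

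The article does not say whether a returned but unscored test is treated differently from one that never came back. The same test is used again at T3, where the percentage score enters the linear mixed model for sustained knowledge.

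**The concern.** Up to three blanks, the plan treats an unanswered item as evidence of not knowing. At the fourth blank the whole returned test loses its score, including the items that were answered. The participant then has no value for the primary outcome or for sufficient knowledge, and the imputation sentence covers both.

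Two things are at stake. For the binary outcome, a result that can be read off the returned form may be replaced by an imputed one that is wrong. For the percentage score, the participant's own answers are set aside and replaced by a value taken from elsewhere, so the estimated difference comes to depend on how often this happens in each arm.

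**Working it through.** **The plan's own figure.** The sample size reproduces. With a difference of 0.085, SD 0.17, two-sided 5% and 90% power, the normal approximation gives 2 × (1.960 + 1.282)² × (0.17/0.085)² = 84.1, so 85 per group. The noncentral t gives power 0.8999 at 85 and 0.9032 at 86, so 86 is right for the t-test. Then 86/0.8 = 107.5, so 108 per group and 216 overall. The point below does not alter this; 0.085 serves only as a yardstick.

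**Sufficient knowledge.** Inputs: 13 items, the 70% cut-off, and no score from four blanks. The highest attainable score with b blanks is (13 − b)/13.

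| Blanks | Most correct | Highest score | Can reach 70%? | Score given? |
|---|---|---|---|---|
| 3 | 10 | 76.9% | yes | yes |
| 4 | 9 | 69.2% | no | no |
| 5 | 8 | 61.5% | no | no |
| 6 | 7 | 53.8% | no | no |

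Passing needs 0.70 × 13 = 9.1, that is, 10 correct answers. The no-score rule starts exactly where passing becomes impossible, so every unscored returned test is a 'no'.

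**Primary score.** The documents give no blank counts, so this part is an illustration on assumed values. Let scored tests average 0.60 in the intervention group (IG) and 0.515 in the control group (CG), a difference of 0.085. Let unscored tests average 0.30 if their blanks were counted as wrong.

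Case 1: 5% of IG tests and 15% of CG tests unscored.
- Blanks as wrong: (0.95 × 0.60 + 0.05 × 0.30) − (0.85 × 0.515 + 0.15 × 0.30) = 0.585 − 0.483 = 0.102.
- Group-mean imputation: 0.60 − 0.515 = 0.085.
- Overall-mean imputation: the mean of scored tests is (0.570 + 0.438)/1.80 = 0.560, giving 0.598 − 0.522 = 0.076.

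Case 2: 5% unscored in both arms.
- Blanks as wrong: 0.585 − 0.504 = 0.081.
- Group-mean imputation: 0.085.
- Overall-mean imputation: 0.598 − 0.517 = 0.081.

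Under group-mean imputation the shift relative to blanks as wrong is (IG share × IG gap) − (CG share × CG gap), where gap is the scored mean minus 0.30. In case 1 this is 0.05 × 0.300 − 0.15 × 0.215 = −0.017. In case 2 it is 0.05 × 0.300 − 0.05 × 0.215 = +0.004. The sign changes with the shares.

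**The case against.** **Withholding a total from a largely incomplete form is a common convention.** The two scoring sentences can be read as one rule with a completeness limit: isolated blanks are wrong, and a form with 4/13 = 31% or more unanswered gets no total. For the percentage score this has force, because extending blank-as-wrong past the plan's limit is partly a choice between conventions. It does not rescue the binary outcome. Someone who answered at most nine of 13 items has at most nine correct, whatever the blanks are called.

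**Imputation of these tests is inferred.** It comes from joining Data collection to Data analysis. The unnamed method might set missing to not sufficient, which would handle the binary outcome correctly, and an analysis plan that is not shown may say so. The absence of a named method is therefore not the complaint. As written, however, no exception is made for returned tests, and the primary score would still be replaced.

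**A reader might infer more:** that the rule removes mainly low-scoring controls, overstates the control mean and pulls the primary effect toward the null. For example, 10% of controls unscored with a gap of 0.20 would raise the control mean by 0.02, or 24% of 0.085. The documents do not support this.
- They give no blank rates by arm.
- They do not list the answer choices, so it cannot be established that a blank stands in for 'don't know'.
- The pilot counts in the Sample size section (15 datasets before training and 12 after, from 16 participants) give no hint of greater loss among the untrained, although the reasons are not stated.
- The 0.02 counts one arm only and rests on assumed inputs. Against the pilot effect of 0.38 it would be about 5%.

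**Scoring all blanks as wrong can also bias the result.** Controls receive the test by mail. If they skip more items through low effort, counting those as wrong inflates the effect. This stands, and it is why the change for the primary score should be an added analysis and not a replacement.

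**Conclusion.** The point holds firmly for sufficient knowledge. Every returned test with four or more blanks is below 70% on a 13-item denominator, so any imputed value other than 'no' is an error. This rests only on the stated item count and cut-off, and on reading the imputation sentence as covering unscored returned tests. How many participants are affected is unknown.

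For the primary score the conclusion is narrower: information in a returned test is discarded and replaced. The bias depends on the share of such tests per arm and on the imputation method, can go in either direction, and cannot be sized from the documents. The illustrative differences show only that the estimate can shift by an amount that is not negligible beside 0.085. They do not predict its direction or size.

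**What to change.** 1. For secondary outcome 1, class any returned test with four or more blanks as not sufficient, at T1 and wherever else the cut-off is applied, and do not impute it. This costs one sentence.
2. For the primary score, keep the current rule and add an analysis that scores all returned tests out of 13 with blanks as wrong and imputes only tests that were not returned. Present the two side by side.
3. Report by arm the number of returned tests with four or more blanks, separately from tests not returned.

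None of this needs new data or changes the sample size. The downside of the added analysis is that a skipped page, or low effort on a mailed test, is scored as lack of knowledge. That could inflate the effect if it is more common among controls. Showing both analyses with the counts by arm lets the reader judge this.
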